##### Card reader

Card readers are installed in all participating intervention and control facilities. The device used is a Famoco Fx100, an android near field communication (NFC) card reader. The Fx100 has an in-built SIM card slot and is enabled for GSM/GPRS/3G communication. The card reader is connected to a remote server that electronically personalizes the NFC card of the user during enrolment, and tracks her subsequent health visits. Each time the *Afya* card makes contact with the reader, the information stored on the card is transmitted to the reader and from the reader to the card, then subsequently from the reader to the web portal (an electronic database) [29]. The card also has an offline transacting capability with the terminal reader that enables it to function during occasional absence of connectivity. The reader also comes with a power back up that enables it to function when there is no electricity for a prolonged duration.

This web portal enables the study team to remotely track participants’ health facility attendance throughout pregnancy and up until 12 months after delivery, and to effect the cash transfer payments. On confirmation of a timely visit, payments to participants are made directly from the project’s bank account where the funds are held, to the participants’ mobile money accounts. This is achieved through integration of the Famaco FX card reader system with Safaricom Bulk Disbursement Service, the leading mobile money payment provider in Kenya. A payout is thus automatically triggered following the touching of the *Afya* card on any of the 48 terminal readers. Manual payouts are triggered by the project team upon verification of visits by participants who forget to carry their clinic books during the visits or who visit non-enrolling facilities that have no readers installed. Pregnant women are therefore not restricted to using the facility at which they were enrolled as long as it is within the study evaluation zone, which is Siaya County. Health visits outside Siaya County are not recorded or rewarded, except for high-risk groups (see Collecting data on visits to facilities outside the study area).

The web portal is continually monitored by a member of the project team to ensure that there are no pending payments for timely health visits attended. The project team also makes regular visits to the health facilities to monitor whether all system components function as expected, and to resolve any challenges promptly.

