### Data collection methods

Data are collected in person by nurses at enrolment, over the telephone by trained interviewers at key time points, and through manual extraction of routine health records supplemented by the electronic contact card system. Data are also collected to facilitate rigorous process and economic evaluations. Table 1 summarizes the data collected using each method.

**Table 1 Tab1:** Primary and secondary outcomes of the trial and sources of these data for different outcomes

Primary outcomes	Source of data
• Proportion of all eligible ANC visits made after recruitment • Delivery at a health facility • The proportion of health appointments honoured for PNC at week 2 to 6 after delivery, and months 4–12 after delivery • Proportion of referrals for ANC, PNC and child immunization attended Proportions of immunization appointments attended by children	• Abstracted health records from the health facility • Electronic system used to enrol participants into the study • Telephone surveys will collect visits made outside the study area by all “high risk” women and 50% of other women
Secondary outcomes	Source of data
• Proportion of women retained in the continuum of MNCH from pregnancy to 12 months post-delivery	• Clinic records • Electronic card system • Telephone survey 3 at 6 months after delivery
• Likelihood of a live birth and child survival 48 h after birth	• Clinic records • Telephone survey 2 at 2 weeks after EDD, if not delivered at the facility
• Likelihood of a maternal death during delivery and 48 h postpartum	• Clinic records • Telephone survey 2, 2 weeks after EDD, if not delivered at the facility
• Self-rated health of mothers, 6 months and 12 months after delivery	• Telephone surveys 1, 3 and 4 at 6 months and 12 months after delivery
• Mother’s perception of infant’s health, 6 months and 12 months after delivery	• Telephone surveys 2, 3 and 4 at 6 months and 12 months after delivery
• Proportion of mothers exclusively breastfeeding to 6 months of age	• Telephone surveys 2 and 3 and 4 at 6 months and 12 months after delivery
• Proportion of women using family planning and contraceptive use after delivery	• Telephone surveys #3 and #4 at 6 months and 12 months after delivery
• Screening and control of infections for mothers and fetus/baby during pregnancy and postnatal periods	• Clinic records (ANC, HF deliveries and PNC clinic records) • Manual collection of health records

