#### Telephone surveys

Data are collected on secondary outcomes, socio-economic characteristics, care seeking and decision-making regarding the cash transfer, using the four follow-up telephone surveys described subsequently. Some data on the primary outcomes are also collected (see Table 1). The surveys are administered to all participants in both the intervention and control groups.

Telephone survey one: after enrolment

The first telephone interview is conducted with all participants as soon as possible after enrolment. This structured questionnaire collects data on socio-economic status, self-rated health and decision-making. Information on the recent health visit is also collected, including cost and time taken to travel to the facility, waiting time, cost of all care received and satisfaction with the care received. The same questionnaire is administered to the intervention and control groups, and the interviewer is blinded to the allocation of the participant.

Telephone survey two: 2 weeks after the EDD, if no facility delivery

A phone survey is conducted with all mothers who delivered babies at home, 2 weeks after their EDD. This survey collects information on delivery date, delivery outcome, who conducted the delivery, self-rated wellness for mother and child and breastfeeding initiation. The interviewer is blind to participant allocation.

Telephone survey three: 6 months after the EDD/child birth

A telephone survey is administered to 50% of participants 6 months after the EDD, to collect data on secondary outcomes such as maternal and child deaths, self-rated health of mothers and infants, exclusive breastfeeding and utilization of family planning methods. This survey also collects information on the last health care visit including the cost of seeking care, purpose of visit, waiting time and visit experience.

A second part of the survey is used to elicit information on the receipt of any conditional or unconditional cash transfer, receipt of *Afya* transfers (in the intervention arm only), how any money received was spent and who decided how the money was spent. The interviewer is not blind to participant allocation, as some questions are related to receipt and utilization of the cash transfers.

Telephone survey four: 12 months after the actual delivery date

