A final survey is conducted with the same 50% of participants who completed telephone survey three. This survey again collects data on secondary outcomes such as maternal and child deaths, self-rated health, breastfeeding and utilization of family planning methods, information on the latest health care visit, and receipt and use of any cash transfers. Moreover, this survey collects additional information on complementary feeding and immunization. The interviewer is blind to participant allocation except for the final part that seeks information on receipt of cash transfers and its usage.

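### Read literally, the 12-month telephone survey goes only to women who completed the 6-month one, so survey-only 12-month outcomes would be conditional on 6-month response

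*Protocol article*

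**What the plan says.** The Telephone surveys section describes four surveys. Its introduction says: "The surveys are administered to all participants in both the intervention and control groups". The paragraph on survey three then says: "A telephone survey is administered to 50% of participants 6 months after the EDD". The paragraph on survey four says: "A final survey is conducted with the same 50% of participants who completed telephone survey three".

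Table 1 (Data collection methods) lists the sources for each outcome:
- For self-rated maternal health the only entry is "Telephone surveys 1, 3 and 4 at 6 months and 12 months after delivery". Perceived infant health and contraceptive use are likewise sourced only from telephone surveys, with survey four supplying the 12-month value.
- For the outcome "Proportion of women retained in the continuum of MNCH from pregnancy to 12 months post-delivery" the entry is "Clinic records • Electronic card system • Telephone survey 3 at 6 months after delivery". Survey four is not listed.

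The Card reader section says that the web portal lets the team "track participants’ health facility attendance throughout pregnancy and up until 12 months after delivery". Under Collecting data on visits to facilities outside the study area, lower-risk women's out-of-area visits are learned from the surveys given to half the participants. High-risk women are followed by separate calls and record extraction.

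**The concern.** The sampled half and the women who completed survey three are the same group only if every sampled woman responds. The survey-four sentence treats them as one group. If field staff follow it as written, one missed call at 6 months removes a woman from the 12-month survey as well.

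This has two consequences. First, interviews that could have been obtained are given up. Second, the remaining 12-month data describe women who answered at 6 months, who may differ from those who did not, for example in mobility. For the three survey-only outcomes no other source can fill the gap. For lower-risk women's out-of-area visits after the 6-month call, survey four is the only scheduled survey that can pick them up. Under Final analysis those reports may be used to impute visits for the remaining women, and the imputed analysis would then be primary.

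Separately, the only telephone source named for retention to 12 months is a 6-month interview, which cannot observe months 6 to 12.

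**Working it through.** **The plan's own figures.** Sample size gives 48 clusters of 150, and 48 × 150 = 7200, or 3600 per arm. Design effect = 1 + (150 − 1) × ICC, which is 1.745 at 0.005 and 4.725 at 0.025. The effective size per arm is 3600/1.745 = 2063 and 3600/4.725 = 762. These agree with the article, and the present point does not depend on them.

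**Survey sample.** Half of 7200 is 3600 women: 1800 per arm, 75 per cluster.

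**Interviews lost under the literal rule.** The documents give no response rates, so these are assumptions: r = share completing survey three (70% to 90%); 90% of completers reached at 12 months; b = share of non-completers reachable at 12 months (30% to 50%).

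- Interviews under the literal rule = 3600 × r × 0.9
- Interviews forgone = 3600 × (1 − r) × b
- Share forgone = forgone / (literal rule + forgone)

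| r | Literal rule | Forgone, b = 30% | Forgone, b = 50% | Share forgone |
|---|---|---|---|---|
| 90% | 2916 | 108 | 180 | 108/3024 = 3.6% to 180/3096 = 5.8% |
| 80% | 2592 | 216 | 360 | 216/2808 = 7.7% to 360/2952 = 12.2% |
| 70% | 2268 | 324 | 540 | 324/2592 = 12.5% to 540/2808 = 19.2% |

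If r = 100%, or if completed means sampled for, the loss is zero.

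**Effect on the arm comparison.** Let d be the outcome difference between 6-month responders and non-responders, equal in both arms. In an arm with response r, responders differ from the whole sampled half by (1 − r) × d. The bias in intervention minus control is therefore (r_control − r_intervention) × d. With d of 10 to 20 points (assumed):

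- 80% in both arms: 0.
- 75% versus 85%: 0.10 × d, or 1 to 2 points in size.
- 70% versus 90%: 0.20 × d, or 2 to 4 points in size.

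For scale, the full sampled half has an effective size per arm of 1800/(1 + 74 × 0.005) = 1314 or 1800/(1 + 74 × 0.025) = 632. From a control proportion of 50% it detects about 55.5% or 57.9% with 80% power (two-sided 5%).

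**Retention row.** Of its three sources, clinic records and the card system do not depend on answering a telephone, and the portal runs to 12 months after delivery. Only the telephone component ends at 6 months.

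**The case against.** The strongest reply is that completed is loose wording. Elsewhere in the article 50% is the share to whom the survey is given, and completers would be exactly that half only with full response, when nobody is lost. Final analysis speaks of telephone data for at most half the lower-risk women, so the authors expect non-response. The Abstract lists contacts at about 6 and 12 months with no condition on the earlier one. Call-back rules may also stand in the full protocol. This makes the loss conditional on the literal reading. It does not remove the point, because nothing in the article says that a woman missed at 6 months is still called at 12.

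Stronger readings are tempting but not supported:

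- A reader might infer that 12-month retention data are lost, or rest on survey three alone. Table 1 also lists clinic records and the card system, which cover all women.
- A reader might infer that mortality outcomes are affected. Survey four asks about deaths, but the listed survival and maternal death outcomes end at 48 hours and come from clinic records and survey two.
- A reader might infer that payment by telephone makes response differ by arm. The amounts differ (Ksh 450 against Ksh 50 of airtime), but controls are paid through the same system and telephone access is required of everyone. Differential response is possible, not shown.
- A reader might infer that the primary analysis is compromised. Out-of-area reports are imputed only if bias seems likely, and the criteria are left to the analysis plan.

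The sub-sampling is a deliberate choice. The Discussion acknowledges it as a limit on power and does not mention selection on 6-month response.

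**Conclusion.** The point holds in a narrow, conditional form. As worded, survey four excludes sampled women who missed survey three. The three outcomes known at 12 months only by telephone, and lower-risk women's late out-of-area reports, would then be conditional on 6-month response. Under the assumed rates this forgoes 108 to 540 interviews, about 4% to 19% of those obtainable; if completed means sampled for, it forgoes none. Fewer interviews do not in themselves bias the arm comparison: that needs response, or its link with outcome, to differ by arm, and the documents neither show nor exclude this. The retention row has a smaller defect, confined to its telephone component. This is an inexpensive improvement and not a threat to the trial's main conclusions.

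**What to change.** 1. In the survey-four paragraph, state that the call is attempted with every woman sampled for survey three who is not known to have died or withdrawn, whether or not she completed survey three.
2. In Table 1, add survey four to the sources for retention to 12 months.
3. In the Telephone surveys section, reconcile the introductory statement that all participants are surveyed with the 50% given for surveys three and four.

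The cost is wording plus extra calls by interviewers already in place. The women to be attempted number 3600 × (1 − r): 360 at 90% completion, 720 at 80% and 1080 at 70%, less known deaths and withdrawals. The change reduces selection on 6-month response but does not remove it, since some of these women will be missed again.

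The change could still take effect at the protocol version date of 26 December 2018 (Trial status). Women enrolled after February 2018, when 2841 of the target 7200 had joined, would have their 12-month call after February 2019.

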#### Manual extraction of health records

At the end of the enrolment period and throughout the remaining trial period, health seeking and health status data will be manually extracted from routine health records held at facilities. Additional file 2 shows the detailed health records that are taken during ANC, delivery and postnatal health visits. A record book is also available at health facilities for each child, and a child growth card is issued to women who deliver at health facilities. This card contains key data on the newborn from birth until they reach 5 years of age.

Towards the end of the trial period, data on health visits and services will also be collected from referral facilities attended by the participants. Data on visits made to health facilities outside Siaya County will not be extracted or rewarded. Participants will be identified in the records by their study ID number^1^ to ensure participant confidentiality.

#### Electronic capture of health visits

A secondary method for collecting data on the primary health outcomes is the electronic card reading system as described previously (see “Card reader”). The system has been designed for the project by an information and communications technology (ICT) company in Kenya called Nailab. The system is fully owned by the project and will only be utilized to fulfill the objectives of the project. Using two primary data collection methods will enable us to triangulate our data and increase confidence in the trial results.

#### Collecting data on visits to facilities outside the study area

The strategies used to collect these data vary according to whether or not the participant is considered high risk. High-risk groups in this study comprise mothers whose ANC records show HIV-positive status, positive malaria smear test and/or other diagnoses of sexually transmitted infection (STI). These diagnoses are likely to require referrals and additional health visits not captured in routine ANC or PNC records. Furthermore, participants with these complications are more likely to be lost to the routine monitoring systems as they might completely shift their ANC, delivery and PNC visits to the referral centers that handle these infections.

We will track all health visits made by high-risk participants only, including those taking place in neighbouring counties outside the evaluation zone. This would be done through extra phone calls to the participants to elicit information on health facilities visited. The study team will then visit those facilities and manually extract health records as described previously. The exception to this case would be if care is sought outside the Western Kenya region, in which case the data will be considered missing in the case of a single instance of care seeking, or the participant will be classed as lost to follow up if they have permanently transferred.

For lower risk participants, we shall incorporate questions relating to the primary outcomes (facility visits, child vaccinations etc.) into the telephone surveys (see Telephone surveys) administered to 50% of participants. This gives participants the opportunity to report visits both outside the study area and within, and we shall also ask whether the participant moved temporarily or permanently outside the study area. By comparing these self-reports with the data on visits within the study area (collected by other means) we will be able to approximately deduce the number of visits made outside the study area. These additional visits will not be verified by the study team as will be done for high-risk participants.

#### Baseline data

In order to understand the baseline characteristics and behaviour of the sample population, a retrospective audit of ANC, delivery and PNC will be undertaken by chart review at selected facilities. The retrospective chart audit entails collection of data from all facilities, between January and December 2016 in the year preceding the commencement of participant enrolment. The data were collected according to a pre-determined proforma. This included data on primary trial outcomes, retention at the local facility and continuity of care. Data were anonymised at collection and each new entry was assigned a unique retrospective *Afya* identifier number.

#### Process evaluation

To inform replication and scale up of the intervention, a mixed method process evaluation is underway to document the design, implementation and mechanisms of the intervention. The process evaluation is aimed at answering the following questions:What factors affect the intervention’s delivery and impact?What are the likely operational requirements for delivering the intervention at scale?How acceptable is the intervention to recipients?What is the impact of the intervention on health staff motivation and job satisfaction?

Quantitative data for the process evaluation are being collected from health records, telephone survey data and *Afya* contact-card data as described previously for the main trial outcomes. Qualitative data for the process evaluation are being collected via key informant interviews with a sub-sample of participating health facility staff, focus group discussions with a sub-sample of participating women in the study area, with sampling to saturation and field notes from intervention team members and notes from the monthly debriefing meeting.

It is also expected that the intervention will increase demand for health services. However, no expansion in health service supply is planned and as such, the increase in demand will likely increase the workload of existing staff. To capture any unanticipated impact on effort, data on health workers’ motivation and satisfaction [35] will be collected in both arms of the trial. A less motivated health worker may perform adequately in minimally demanding conditions, but their willingness to exert extra effort might depend on whether they feel there is personal value in doing so [36]. Further, if a workplace is not conducive to effective working, or if health workers do not have the knowledge, skills or experience to complete their tasks, they might be demotivated. Thus, health worker motivation is the ability and willingness to put in the effort required to do the job, influenced by individual factors (such as knowledge, skills, experiences, psychological attributes) and organisational factors (such as physical and social environment, policies and practices) [37]. Organisational factors are more likely to change than individual personality tendencies, or societal and cultural values. Thus, with the introduction of the card system and the potential increase in the demand for MNCH services, health worker motivation is likely to be affected, with consequences for service delivery. A self-completion motivation and job satisfaction survey will thus be administered to all participating health staff. Collecting and analysing these data will allow us to explore how the intervention could affect health worker motivation and satisfaction [38], and potentially service delivery.

#### Economic evaluation

An economic evaluation will be conducted from the provider perspective. Costs incurred by implementing agencies will be collected prospectively from the project accounts and input into a customised Excel-based costing tool. Data on healthcare provider costs will be collected retrospectively from a random sample of participating health facilities in the control and intervention arms. Data on resource use for maternal and child services, including equipment, drugs, floor space, overheads and the time input of health facility staff, will be collected using key informant interviews with healthcare providers and financial controllers [39–41]. These data will be supplemented with information on participants’ health-seeking behaviour and utilization, collected through the card reader and follow-up phone surveys.

All costs will be adjusted for inflation using the Kenyan Consumer Price Index (CPI) and presented in international dollars. The incremental cost-effectiveness of the *Afya* intervention will be compared with the status quo alternative. Incremental cost-effectiveness ratios (ICERs) will be calculated for all statistically significant primary trial outcomes, as well as selected significant secondary outcomes. In addition to ICERs, results will be presented as a cost-consequence analysis [42, 43], listing all costs and outcomes separately, allowing policymakers to compare the costs and impacts of the *Afya* intervention.

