**Methods:**

The intervention tested is a conditional cash transfer to women for ANC health visits, a facility birth and PNC visits until their newborn baby reaches 1 year of age. The study is a cluster randomized controlled trial in Siaya County, Kenya. The trial clusters are 48 randomly selected public primary health facilities, 24 of which are in the intervention arm of the study and 24 in the control arm. The unit of randomization is the health facility. A target sample of 7200 study participants comprises pregnant women identified and recruited at their first ANC visit over a 12-month recruitment period and their subsequent newborns. All pregnant women attending one of the selected trial facilities for their first ANC visit during the recruitment period are eligible for the trial and invited to participate. Enrolled mothers are followed up at all health visits during their pregnancy, at facility delivery and for a number of visits after delivery. They are also contacted at three additional time points after enrolling in the study: 5–10days after enrolment, 6 months after the expected delivery date and 12 27 months after birth. If they have not delivered in a facility, there is an additional follow-up 2 wees after the expected due date. The impact of the conditional cash transfers on maternal healthcare services and utilization will be measured by the trial’s primary outcomes: the proportion of all eligible ANC visits made during pregnancy, delivery at a health facility, the proportion of all eligible PNC visits attended, the proportion of referrals attended during the pregnancy and the postnatal period, and the proportion of eligible child immunization appointments attended. Secondary outcomes include; health screening and infection control, live birth, maternal and child survival 48 h after delivery, exclusive breastfeeding, post-partum contraceptive use and maternal and newborn morbidity. Data sources for the measurement of outcomes include routine health records, an electronic card-reader system and telephone surveys and focus group discussions. A full economic evaluation will be conducted to assess the cost of delivery and cost effectiveness of the intervention and the benefit incidence and equity impact of trial activities and outcomes.

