#### Secondary outcomes

The secondary outcomes are:Proportion of women retained in the continuum of MNCH from pregnancy to 12 months post-deliveryLikelihood of a live birth and child survival 48 h after birthLikelihood of maternal death during delivery and 48 h postpartumSelf-rated health of mothers at 6 months and 12 months after deliveryMother’s perception of infant’s health 6 months and 12 months after deliveryProportion of mothers exclusively breastfeeding to 6 months of ageProportion of women using family planning or contraceptives after deliveryScreening and control of infections for mothers and fetus/baby during pregnancy and postnatal periodsCost of delivery and cost effectiveness of the interventionBenefit incidence and equity impact of the intervention

Process evaluation [34] will document the design, implementation and mechanisms of the intervention. A full economic evaluation will be conducted to assess the cost of delivery and cost effectiveness of the intervention and the benefit incidence and equity impact of trial activities and outcomes.

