### Sample size

We hope to analyse all the primary outcomes jointly and also to analyse most outcomes as ordinal variables (see Data management and analysis), thereby maximising power and aiding interpretation. However, for our sample size calculation, we consider power to detect an effect of the intervention on one primary outcome, which we also assume to be a binary indicator that all attendances are made, as this is simple and conservative in the power achieved. The expected prevalence of these indicators in the control arm ranges between 30 and 80%. Little specific information on the likely intra cluster correlation (ICC) for any of the outcomes is currently available - we consider it may lie between 0.005 (low) and 0.025 (moderate). Our planned sample size is 48 clusters (24 per arm) and an average cluster size of 150. At a low ICC, the design effect (DE) will be 1.745 and hence the effective sample size (ESS) will be 2063 participants per study arm. At a moderate ICC, the DE will be 4.725 and hence the ESS will be 762 per arm. Power to detect absolute differences is lowest when the prevalence is 50% and highest when the prevalence is either high (towards 100%) or low (towards 0%). Here we consider the prevalence in the control arm to range between 50% (‘worst-case scenario’) and 80% (‘best-case scenario’). We consider the standard 5% significance level. If the prevalence of the outcome is 50% in the control arm, the sample size provides 80% power to detect an improvement to 54.5% in the intervention arm if the ICC is low and 57.5% if the ICC is moderate. If the prevalence of the outcome is 80% in the control arm, the sample size provides 80% power to detect an improvement to 83.5% if the ICC is low and 85.5% if the ICC is moderate.

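### ICERs are to be calculated only for statistically significant outcomes, which withholds the ratio from the others and overstates on average the effect behind favourable ICERs that are reported

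*Protocol article*

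**What the plan says.** The protocol article, Economic evaluation, states the rule directly: "Incremental cost-effectiveness ratios (ICERs) will be calculated for all statistically significant primary trial outcomes, as well as selected significant secondary outcomes". The comparison is defined just before it: "The incremental cost-effectiveness of the *Afya* intervention will be compared with the status quo alternative". The next sentence adds a presentation that carries no significance condition: "In addition to ICERs, results will be presented as a cost-consequence analysis [42, 43], listing all costs and outcomes separately".

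Elsewhere the economic question is unconditional. The Methods paragraph of the abstract promises that "A full economic evaluation will be conducted to assess the cost of delivery and cost effectiveness of the intervention", and the Secondary outcomes list includes the "cost of delivery and cost effectiveness of the intervention" with no reference to a test result. For the test itself, the Sample size section says "We consider the standard 5% significance level".

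**The concern.** An ICER divides an incremental cost by an incremental effect. The rule lets the ratio exist only if the estimated effect passes a significance test in the same data. Two things follow.

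- **Missing ratios.** An outcome that narrowly misses the threshold gets no ICER. Yet failing to reject no effect is not evidence that the intervention is poor value. That depends on costs and effects jointly, with their uncertainty. If no primary outcome were significant, the rule as written would give no ICER for any of them.
- **Selected estimates.** A favourable effect that has passed the filter is too large on average, so the ratio built on it tends to look too cheap unless power is high.

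For secondary outcomes there is a second filter: the outcome must be significant and then also be selected, on grounds that the article does not state. At stake is the usefulness of the ICERs to the policymakers for whom the section says the economic results are meant.

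**Working it through.** **Inputs from the Sample size section.** "Our planned sample size is 48 clusters (24 per arm) and an average cluster size of 150", so 24 × 150 = 3600 women per arm. The ICC is taken to lie between 0.005 and 0.025. The significance level is 5%; two-sided testing is assumed here.

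**The plan's own figures.** DE = 1 + (150 − 1) × ICC, and ESS = 3600 / DE.

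- ICC 0.005: DE = 1.745, ESS = 2063 per arm.
- ICC 0.025: DE = 4.725, ESS = 762 per arm.

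Both match the article. The improvements detectable with 80% power come out at 54.4% and 57.2% (control 50%) and at 83.4% and 85.4% (control 80%). The stated 54.5%, 57.5%, 83.5% and 85.5% are these values rounded up to the next half point. The sample size calculation is not in question.

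**How large an effect must be to earn an ICER.** The smallest significant difference is 1.96 × SE, with SE = √[(p0(1 − p0) + p1(1 − p1)) / ESS]. For control 50%, a true gain of 3 points and ESS 762, SE = √[(0.2500 + 0.2491) / 762] = 0.0256, which gives 5.0 points. At ESS 2063 it is about 3.0 points.

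**Overstatement of the effect after selection.** Let X ~ N(z, 1) be the standardised estimate, with z = 1.96 + Φ⁻¹(power). Given a favourable significant result, E[X | X > 1.96] / z = 1 + φ(1.96 − z) / (z × power).

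- Power 80%: z = 2.802; 1 + 0.2800 / (2.802 × 0.8) = 1.12.
- Power 50%: z = 1.960; 1 + 0.3989 / (1.960 × 0.5) = 1.41.
- Power 30%: z = 1.436; 1 + 0.3477 / (1.436 × 0.3) = 1.81.

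**Effect on the ICER.** With a fixed positive cost increment, the mean of reported ICER / true ICER is E[z / X | X > 1.96]. This was found by simulation with 1,000,000 draws:

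| True power | Mean effect ratio | Mean ICER ratio |
|---|---|---|
| 30% | 1.81 | 0.57 |
| 50% | 1.41 | 0.74 |
| 80% | 1.12 | 0.94 |
| 90% | 1.06 | 1.00 |

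The mean ICER is thus about 43%, 26% and 6% too low at 30%, 50% and 80% power, and not too low at 90%. The reciprocals of the mean effect ratios (0.55, 0.71 and 0.89) would overstate the bias, because the mean of a reciprocal exceeds the reciprocal of the mean.

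**In the trial's own terms.** At the four stated design improvements, power is 81% to 84%, the effect is overstated 1.10 to 1.12 times, and the mean ICER ratio is 0.95 to 0.96. For smaller true effects the distortion grows. A true gain from 50% to 53% is significant 22% of the time at ICC 0.025, and the estimate then averages 2.16 times the truth (mean ICER ratio 0.48). At ICC 0.005 the same gain is significant 49% of the time and overstated 1.42 times (mean ICER ratio 0.73).

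**How often a ratio would be missing.** If each of the five primary outcomes had 80% power and they were independent (an assumption; they are likely to be correlated), the chance that at least one gets no ICER is 1 − 0.8⁵ = 67%.

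**The case against.** The strongest reply has four parts.

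1. **The bias is small where the trial is designed to operate.** This stands. It is about 6% on the mean ICER at 80% power and absent at 90%. A reader might infer that every reported ICER will be too low. The calculation does not support that, and the article does not say that true power will be as low as 30% or 50%. It does say that little is known about the ICC, so lower power on some outcomes cannot be ruled out either.

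2. **Costs are not fixed.** This also stands. The Cash transfer value section pays Ksh 450 for each timely visit, so a high attendance estimate tends to go with a higher cost. That offsets part of the bias, by an amount that cannot be derived without cost data.

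3. **Nothing is hidden.** A reader might infer that the rule drops unfavourable outcomes from the report. It does not: the cost-consequence analysis lists all outcomes beside the costs. What is lost is the ratio and its uncertainty.

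4. **Cost-effectiveness is secondary.** The Research questions section places it among the secondary objectives, although the Background also names it as something the trial is testing. This bears on priority and does not make the rule sound.

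A reader might also see a contradiction with the Final analysis section, where a summary odds ratio across the primary outcomes is the primary effect measure. That reading is weak. The same section first states tests of the individual primary outcomes, and presenting a pooled odds ratio does not prevent the economic evaluation from using outcome-level effects.

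**Conclusion.** The rule is wrong as written. This is a stated condition, not a detail left to an unseen analysis plan. Its surest consequence is that outcomes which miss significance get no ICER, whatever their costs and effects suggest. Its second is an average overstatement of the effect behind any favourable ICER that is reported: 12%, 41% and 81% at true power of 80%, 50% and 30%, assuming a normally distributed estimate and a two-sided 5% test.

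The consequence for the ICER itself is less certain. The figures of 6%, 26% and 43% too low rest on a fixed positive cost increment. They are averages rather than predictions for a single result, and payment per visit would shrink them. The point should be corrected, but it does not touch the trial's primary effect analysis.

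**What to change.** Replace the sentence on ICERs with wording such as: *Incremental costs, incremental effects and ICERs will be calculated for all primary outcomes and for a prespecified list of secondary outcomes, irrespective of statistical significance, with uncertainty in costs and effects reported and clustering respected as far as the sampled facility cost data allow.* Keep the cost-consequence analysis.

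The last clause matters because provider costs come from only a random sample of participating facilities, so a joint resampling of costs and effects over all 48 clusters is not directly available. The particular method for showing uncertainty can be left to the analysis plan.

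The cost is a little extra analysis. Some ICERs will be imprecise or will rest on effects whose intervals include zero, and they should be reported as such.
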